### APPENDIX 3.

**Table 1. Grading scale for determining the severity of adverse events:**

| Clinical sign/symptom | Grade 1                                                 | grade 2                                                                        | grade 3                                                                  | grade 4                                                                  |
|-----------------------|---------------------------------------------------------|--------------------------------------------------------------------------------|--------------------------------------------------------------------------|--------------------------------------------------------------------------|
| Abdominal pain (2)    | Mild                                                    | Moderate- no treatment needed                                                  | Moderate- treatment needed                                               | Severe- hospitalization for treatment                                    |
| Nausea (1)            | Mild discomfort; maintains reasonable intake            | Moderate discomfort; intake decreased significantly; some activity limited     | Severe discomfort; no significant intake; activities limited             | Minimal fluid intake                                                     |
| Vomiting (2)          | 1 episode/day                                           | 2-3 episodes/day                                                               | 4-6 episodes/day                                                         | Greater than 6 episodes/day or intractable vomiting                      |
| Diarrhoea (2)         | Slight change in consistency and/or frequency of stools | Liquid stools                                                                  | Liquid stools greater than 4x the amount or number normal for this child | Liquid stools greater than 8x the amount or number normal for this child |
| Anorexia (2)          | -----                                                   | Decreased appetite                                                             | Appetite very decreased, no solid food taken                             | No solid or liquid taken                                                 |
| Fever, oral (1)       | 37.7 – 38.5 C or 100.0 – 101.5 F                        | 38.6 – 39.5 C or 101.6 – 102.9 F                                               | 39.6 – 40.5 C or 103 – 105 F                                             | > 40.5 C or > 105 F                                                      |
| Headache (1)          | Mild, no therapy required                               | Transient, moderate; therapy required                                          | Severe; responds to initial narcotic therapy                             | Intractable; required repeated narcotic therapy                          |
| Dizziness (3)         | Not interfering with function                           | Interfering with function, but not interfering with activities of daily living | Interfering with activities of daily living                              | Bedridden or disabling                                                   |
| Allergic reaction (1) | Pruritus without rash                                   | Localized urticaria                                                            | Generalized urticaria; angioedema                                        | Anaphylaxis                                                              |

Adapted from (1) WHO Toxicity Grading Scale, (2) Division of Microbiology and Infectious Diseases (DMID/NIH) Pediatric Toxicity Tables, and (3) National Cancer Institute (NCI) Toxicity Grading Scale.

**Table 2. Severity grading for other Adverse Events will be estimated as follows:**

|                |                                                                                                                                                                                        |
|----------------|----------------------------------------------------------------------------------------------------------------------------------------------------------------------------------------|
| Grade 1 | Mild. Transient or mild discomfort (< 48hs); no medical intervention/therapy required                                                                                           |
| Grade 2 | Moderate. Mild to moderate limitation in activity – some assistance may be needed; no or minimal medical intervention/therapy required                                          |
| Grade 3 | Severe. Marked limitation in activity, some assistance usually required; medical intervention/therapy required, hospitalization possible                                        |
| Grade 4 | Life-threatening. Extreme limitation in activity, significant assistance required; significant medical intervention/therapy required, hospitalization or hospice care probable. |

## APPENDIX 4.

### Classification according to Relationship to the treatment:

**Not related:** The event is clearly related to other factors such as the patient's clinical state, therapeutic intervention or concomitant therapy.

**Unlikely:** The event was most probably produced by other factors such as the patient's clinical state, therapeutic intervention or concomitant therapy and does not follow a known response pattern to the trial product

**Possible:** The event:

- follows a reasonable temporal sequence from the time of product administration; *and/or*
- follows a known response pattern to the trial product; *but*
- could have been produced by other factors such as the patient's clinical state, therapeutic intervention or concomitant therapy.

**Probable:** The event:

- follows a reasonable temporal sequence from the time of product administration, *and/or*
- follows a known response pattern to the trial product, *and*
- could have been produced by other factors such as the patient's clinical state, therapeutic intervention or concomitant therapy.

**Most probable:** The event:

- follows a reasonable temporal sequence from the time of product administration *and/or*
- follows a known response pattern to the trial product, *and*
- could have been produced by other factors such as the patient's clinical state, therapeutic intervention or concomitant therapy, *and*
- either occurs immediately following trial product administration, or improves on stopping the product or there is positive reaction at the application site.

**Insufficient data to assess:** There is not enough clinical and/or laboratory information to suggest the relationship of the event to the trial product.

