## **8. ASSESSMENT OF SAFETY:**

### **Adverse Events**

#### **8.1. Parameters to be measured:**

Occurrence and severity of Adverse Event at 4 hours, 24hs, and 21 days after treatment.

**8.2. Methods:** All AEs will be characterized for: severity grading, relationship to the treatment and seriousness.

Treatment with PZQ will be done in the morning of D0 and the research team will remain at the treatment centre until 18.00 hr. Children administered with PZQ will be observed for at least 4 hours before leaving the school compound.

All schoolchildren enrolled in the study will be administered with a questionnaire 4 hours after treatment for the following signs and symptoms: abdominal pain, nausea, vomiting, diarrhoea, anorexia, fever, headache, dizziness and allergic reaction. Each symptom will be graded as described in Table 1 of Appendix 3. Other symptoms not listed in Table 1 will be graded for severity according to classification in Table 2 of Appendix 3. Also, causal assessment for the adverse events in relation to the drug will be done as: not related, unlikely, possible, probable, most probable or insufficient data to assess (see definitions in Appendix 4). On the following day (Day 1), that is, 24 hours post-treatment, all schoolchildren who received PZQ on Day 0 will be interviewed using the same questionnaire to determine whether they experienced any adverse events. The questionnaire will be repeated on day 21-post treatment. In addition, on day 21 Hb will be measured by digital hemoglobinometer (hemocue) to determine whether increased dosage of PZQ has adverse effects on haemoglobin level.

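### Appendix 4 gives *Possible* and *Probable* the same criteria, and no causality category accepts an adverse event that has no alternative cause

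*Protocol*

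**What the plan says.** Section 8.2 of the protocol requires a causality assessment of adverse events on a six-category scale: "not related, unlikely, possible, probable, most probable or insufficient data to assess (see definitions in Appendix 4"). Three of the six (*Possible*, *Probable*, *Most probable*) express a relation to the drug.

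Appendix 4 builds these three from shared criteria:

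- the event "follows a reasonable temporal sequence from the time of product administration";
- and/or it "follows a known response pattern to the trial product";
- and it "could have been produced by other factors such as" the child's clinical state or other treatment.

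*Most probable* adds one more condition: immediate onset, improvement when the product is stopped, or a reaction at the application site. *Not related* and *Unlikely* attribute the event to other factors. *Insufficient data to assess* is reserved for a lack of clinical or laboratory information. No other section changes these definitions.

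**The concern.** A causality scale should become more certain as it rises, and the usual way is for the alternative explanation to recede. Here the alternative explanation stays as a requirement at every related level. Two things follow if the text is applied as written. Assessors have no criterion that separates *Possible* from *Probable*. And an event with a clear time course and no other explanation, the case most attributable to the drug, has nowhere to go.

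The scale is in use, not background. Section 8.2 makes it part of the record of every adverse event. The same section ties two duties to a likely relation to the product: follow-up of events that persist to the end of the trial, and follow-up of serious events that occur after it. The 24-hour reporting sentence then refers back to serious events of that kind, so reporting may depend on relatedness as well.

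**Working it through.** No sample size or test is involved and the plan states no figure to reproduce. The check is one of logic.

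**Inputs, all from Appendix 4.** T = plausible time course; K = known response pattern; O = other factors could have caused the event; I = the extra condition of *Most probable*.

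| Level | First part | Link | Other-factors criterion | Extra |
|---|---|---|---|---|
| *Possible* | T and/or K | but | O required | none |
| *Probable* | T and/or K | and | O required | none |
| *Most probable* | T and/or K | and | O required | I required |

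In logic *but* and *and* are the same connective, so:

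- *Possible* = (T or K) and O
- *Probable* = (T or K) and O
- *Most probable* = (T or K) and O and I

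**Enumeration.** Four yes/no criteria give 2 × 2 × 2 × 2 = 16 combinations. T or K holds in 3 of the 4 combinations of T and K.

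- *Possible* is met in 3 × 1 × 2 = 6 of 16.
- *Probable* is met in the same 6, so the two levels agree in all 16.
- *Most probable* is met in 3 × 1 × 1 = 3 of 16, all of which also meet *Possible* and *Probable*.
- O is false in 2 × 2 × 2 = 8 of 16. A related level is met in 0 of these 8, even when T, K and I all hold. In 3 × 2 = 6 of the 8, a time course or known pattern is present.

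If assessors record the highest level met (a convention the protocol does not state), *Possible* would never be used, because every event that meets it meets *Probable* too. Without that convention the choice between the two is arbitrary.

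**The remaining three categories when O is false.** *Not related* needs a clear other cause and *Unlikely* a most probable other cause, so both fail. *Insufficient data to assess* needs missing information, which is not the situation. The event meets none of the six definitions.

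**With the criterion negated in the two upper levels.** *Probable* becomes (T or K) and not O, which is 3 × 1 × 2 = 6 combinations, none shared with *Possible*. *Most probable* becomes the 3 of those 6 in which I holds. All 6 combinations that had a time course or pattern but no category now have one. The other 2 with O false have neither T nor K and were never candidates for a related level.

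These are counts of logical cases, not of expected events.

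**The case against.** A reader might infer that the defect understates drug-related harm in the comparison of the two doses. The documents do not support that. Secondary endpoint b in section 3.2, the analysis in section 8.3 and the tests in section 10.1 all concern the frequency and severity of adverse events, with no filter on relatedness. Severity is graded by Appendix 3, independently of Appendix 4. A miscoded event still counts in its arm with its grade.

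The effect on follow-up is also narrower than it may seem. Section 8.2 has every adverse event followed until it resolves, whatever its cause, and seriousness under Appendix 5 has no causality criterion. Where relatedness does matter, the trigger is a likely relation, which is not itself one of the Appendix 4 categories.

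Nor does the defect spoil the coding of every event. *Not related*, *Unlikely* and *Insufficient data to assess* remain usable, and *Most probable* is set apart by its extra condition. Events with no conceivable other cause may be uncommon: every child enters with at least 100 eggs per gram (section 4.1), and the child's clinical state is a listed other factor. The documents give no frequency for such events.

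Finally, an experienced physician may guess what was meant from the labels alone. That is so, but assessors may guess differently, and the record would then not follow the written definitions.

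All of this limits the consequences. None of it removes the defect in the text.

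**Conclusion.** The definitions are wrong as written. Two of the three related levels are logically identical, and an event without an alternative cause fits none of the six categories. The effect is confined to the causality coding required by section 8.2 and to the provisions there that turn on a likely relation to the product: events persisting to the end of the trial, serious events after it, and arguably the reporting of such serious events. The comparison of frequency and severity between arms is unaffected. A correction is warranted, but no stated endpoint or test depends on it.

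Two further inferences should not be drawn. One is that unclassifiable events would be coded as *Insufficient data to assess*: that definition does not fit them, and nothing directs assessors to it. The other is that a *not* was certainly dropped. That is plausible, because *and* joins the clause as if it supported relatedness, but it remains an inference. The affirmative wording stands in both upper levels, so loss in reading the PDF is an unlikely explanation.

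The conclusion assumes only that assessors apply Appendix 4 as it reads.

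**What to change.** In Appendix 4, reword the other-factors criterion in *Probable* and *Most probable* so that the three related levels are distinct and an event without another explanation can be classified. One wording that does this is that the event could not have been produced by other factors. Leave *Possible* unchanged. Make the change before the first D0 assessment, so that all events are coded on one scale. The cost is a few words in one appendix. No endpoint, test or sample size changes.

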## APPENDIX 5.

### Evaluation of seriousness:

#### *Definition of Serious Adverse Event (SAE)*

A serious adverse event is any untoward medical occurrence that, at any dose, has one or more of the following:

- ✓ *results in death,*
- ✓ *is life-threatening\*,*
- ✓ *requires inpatient hospitalization or prolongation of existing hospitalization,*
- ✓ *results in persistent or significant disability/incapacity, or*
- ✓ *is a congenital anomaly/birth defect.*

*\*Note:* the term “life-threatening” in the definition of “serious” refers to an event in which the patient was at risk of death at the time of the event; it does not refer to an event which hypothetically might have caused death if it were more severe

Important medical events that may not be immediately life threatening or does not directly result in death or hospitalization but may jeopardise the patient or may require intervention to prevent on of the other outcomes listed above should also usually be considered as serious.

